### Follow-up

The follow-up time for included patients is 2 years (Figs. 3 and 4) with assessment within 1 week and at 3 months, 6 months, 1 and 2 years from the day of the surgery and thereby randomization. There will be conceived data on complications including revision surgery from medical records and hospital database after 10 years.

### Protocol violations, revision and drop-out

If the surgeon during the surgery regards it as impossible to insert a glenoid component, the surgery can be converted to a stemmed hemiarthroplasty using the DELTA Xtend humeral stem and a CTA head.

If patients drop out of the trial, it will be recorded along with the reason for drop-out. The patient in question will be included in the final mixed-effect model analysis, except for patients who drop out before 3 months, who cannot be included in the analysis. At the end of the study, a sensitivity analysis will be performed to evaluate the impact of missing data on the overall results of the trial. It will be recorded if there are indications that some patients do not comply with rehabilitation.

In case of revision surgery, reason and new arthroplasty type will be recorded. Additionally, the patient will prior to revision surgery be assessed by DXA, radiostereometric analysis, patient-reported outcome and clinical outcome if possible. The patient will stay included in the study and the 2-year analysis with the latest follow-up.

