### Outcome measures

#### Primary radiological outcome

Migration of the glenoid components is assessed by model-based radiostereometric analysis, which is performed according to the guidelines of Valstar and Colleagues [12]. In this part of the study, the first 56 patients are included. Maximum total point motion (MTPM) after 2 years of follow-up is compared to the baseline value and is used as the primary radiostereometric analysis effect parameter. The accuracy of radiostereometric analysis will be assessed by at least 12 double examinations. The reference examination will be done within 1 week after the surgery, and the follow-up examinations are planned at 3 months, 6 months, 1 year and 2 years. Radiostereometric analysis is conducted using a uniplanar radiostereometric analysis arrangement (UmRSA®- Calibration Cage No 43 (hip, spine and shoulder)). The x-ray analysis is performed using the model-based radiostereometric analysis commercial software (RSAcore, Department of Orthopedics, Leiden University Medical Center, Leiden, The Netherlands), available at the Skaane University Hospital, Lund Sweden, where the analyses of radiostereometric analysis-x-rays will be conducted. The exact set-up for the radiostereometric analysis (e.g. various distances and the degree between the 2 x-ray tubes) will be specified from a small phantom study and measurements of the 6 pilot patients (3 with each of the 2 types of implants). 42 combined CAD models for MB-RSA will be delivered by Depuy Synthes (Raynham, MA, USA).

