### Statistics

Prior to the analysis, the nature of the data is assessed. It is expected to analyse the changes between pre- and postoperative assessment with paired parametric statistics. The differences between the groups are expected to be analysed using parametric statistics (Student *t*-test). The radiostereometric analysis data is not expected to be normally distributed and will be analysed using non-parametric analysis of variance over time. The differences between these groups will be analysed with Mann-Whitney *U* test. Because of the nature of repeated measures in this study, it is expected to use a mixed effects model to analyse the overall results. Data on radiostereometric analysis and DXA will be analysed at the end of follow-up for the first 56 patients. No other interim data-analysis will be carried out.

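### Revised patients enter the 2-year analysis with their latest follow-up: this probably understates migration, can bias WOOS either way, and does not fit the planned mixed model; WOOS also loses randomised patients who leave early

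*Protocol article*

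**What the plan says.** The rules stand in the protocol article, section *Protocol violations, revision and drop-out*.

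- **Revision.** Before the operation, "the patient will prior to revision surgery be assessed by DXA, radiostereometric analysis, patient-reported outcome and clinical outcome if possible". Then: "The patient will stay included in the study and the 2-year analysis with the latest follow-up".
- **Drop-out.** Patients who leave are kept in the final mixed-effects analysis, "except for patients who drop out before 3 months, who cannot be included in the analysis".
- **Missing data.** At the end, "a sensitivity analysis will be performed to evaluate the impact of missing data on the overall results of the trial". No method is given.

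The section *Statistics* adds that "it is expected to use a mixed effects model to analyse the overall results". For the radiostereometric data, "The differences between these groups will be analysed with Mann-Whitney" U test.

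Both co-primary outcomes are fixed at 2 years. Under *Primary radiological outcome*, "Maximum total point motion (MTPM) after 2 years of follow-up is compared to the baseline value". Under *Primary functional outcome*, the WOOS contrast is the change from the preoperative to the 2-year score. Revision, meaning removal or exchange of any component, is recorded under *Secondary functional outcomes*.

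**The concern.** A 2-year endpoint calls for a 2-year value. The revision rule seems to accept an earlier value in its place, for the patients in whom the implant or the operation has failed.

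For MTPM, the index glenoid component can no longer be followed once it has been removed or exchanged. If it would have gone on migrating, an earlier value falls short. If the pre-revision film could not be taken, the value used may predate the failure altogether. The trial hopes to show that lateralization does not increase migration or loosening, so understating migration in an arm with more failures favours that conclusion.

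For WOOS, the patient stays in the study and can still answer the questionnaire at 2 years. Replacing that answer with an earlier one departs from the endpoint's own definition. It also sits badly with a mixed model, which takes each score at the visit where it was given.

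The early drop-out rule removes randomised patients because of something that happened after randomisation, although *Enrolment* has them complete WOOS before surgery.

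**Working it through.** **1. The plan's own figures.** Inputs come from the two sample size sections; a two-sided 5% level is assumed. Per arm, n = 2(1.960 + 1.282)² × (SD/difference)² = 21.01 × (SD/difference)².

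- MTPM: SD 0.4, difference 0.4 mm. 21.01 × 1 = 21.01, so 22 per arm as stated. 22/0.8 = 27.5, so 28 per arm and 56 in total, as stated.
- WOOS: SD 15, difference 10. 21.01 × 2.25 = 47.3, so 48 per arm as stated. 48/0.8 = 60 per arm, 120 in total; the plan has 122, slightly more.

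The sample sizes reproduce and are not in question. They supply the yardsticks: 0.4 mm and 10 points.

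**2. Bias in a mean difference from a carried value.** Bias = (excess share revised in one arm) × (true 2-year value minus carried value). No revision rate is given, so the shares of 2%, 5% and 10% are assumptions, as are the amounts missed.

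| Outcome | Smallest case | Largest case | Share of target |
|---|---|---|---|
| MTPM, 0.2 to 2.0 mm missed | 0.02 × 0.2 = 0.004 mm | 0.10 × 2.0 = 0.20 mm | 1% to 50% |
| WOOS, carried score 20 to 30 points too good | 0.02 × 20 = 0.4 | 0.10 × 30 = 3.0 | 4% to 30% |
| WOOS, carried score 20 to 30 points too bad | −0.4 | −3.0 | 4% to 30%, opposite sign |

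The MTPM row has one sign only if migration would have continued to 2 years. The WOOS rows have both signs because a score taken just before revision describes a failing shoulder. It may be worse than the score the patient reports at 2 years after revision.

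**3. Effect on the planned rank test.** A simulation with assumed inputs used 28 per arm, skewed MTPM, a true shift of 0.2 mm and failures that miss 2 mm. Failure rates were 10% against 2%. With failures counted, the mean difference was 0.36 mm and Mann-Whitney rejected in 84% of runs. With pre-failure values carried, these were 0.20 mm and 79%. The estimate suffers more than the test.

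A ceiling for the rank test: with 22 per arm, moving one patient from above to below everyone in the other arm changes P(lateralized > standard) by 22/(22 × 22) = 1/22 = 4.5 points. The powered effect is Φ(1/√2) − 0.5 = 0.76 − 0.50 = 26 points. Three such patients in one arm would give 3/22 = 13.6 points. If their carried values fell at the median instead, the shift would be 6.8.

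**4. Early drop-outs and WOOS.** Assume four early losses in one arm of 61, each 25 points worse than the rest. Leaving them out biases that arm's mean by 4/61 × 25 = 1.6 points. Putting their preoperative score into the model does not remove this. Take a common preoperative mean m and one 2-year outcome. The fitted 2-year mean in each arm is the completers' mean minus b × (completers' preoperative mean − m). In the difference between arms m cancels, and b comes from completers only. Baseline-only patients therefore leave the treatment estimate where it was.

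**The case against.** The strongest reply is that carry-forward is only one reading. A revised patient stays in the study, so the latest WOOS follow-up could be the real 2-year visit, and then the rule is harmless for WOOS. This stands as a possibility. But the sentence follows directly on the pre-revision assessment, and a rule that permits both readings still has to be rewritten.

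Three stronger inferences are tempting, and the document does not support them.

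- *Failure is understated in both co-primary outcomes.* A pre-revision patient-reported assessment is planned, so the WOOS error can go either way.
- *A loose glenoid can be scored as zero migration from the 1-week film.* *Primary radiological outcome* calls that film the reference examination and lists follow-up from 3 months on. It is not a natural latest follow-up.
- *The 3-month rule removes failed implants.* Revision and drop-out have separate rules, and a patient revised before 3 months stays in. That early losses follow complications is an assumption.

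It is also fair to say that a patient lost before 3 months has no follow-up MTPM, so for that outcome the exclusion states a fact. Failures remain visible elsewhere: revisions and their reasons are recorded, complications are a secondary outcome, and *Follow-up* collects revisions after 10 years. This keeps the information in the trial but does not correct the co-primary comparison. Finally, giving failures the worst rank in the primary analysis would turn measured migration into a composite, so it belongs in a sensitivity analysis. The method of the missing-data analysis may properly stand in an analysis plan that is not shown.

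**Conclusion.** The concern holds in limited form. The revision rule, on its natural reading, puts an earlier value in place of a 2-year endpoint and is not reconciled with the mixed model. For MTPM the likely direction is understatement, provided migration would have continued and the glenoid component was the part removed or exchanged. For WOOS the direction is open. The early exclusion departs from analysing all randomised patients for WOOS only.

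The size cannot be known from the document. Under the assumed ranges it runs from negligible to half of the MTPM target and to three-tenths of the WOOS target. The 13.6-point rank shift is an extreme case: it needs three failures in one arm, each moved from the top of the ranking to the bottom. It should not be read as an expected effect.

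**What to change.** Rewrite the revision and drop-out rules before any unblinded comparison.

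- **WOOS.** Use the observed 2-year score whether or not the patient was revised. Analyse all randomised patients as randomised in the mixed model, with preoperative WOOS as the first repeated measure. Keep last-value carry-forward as a sensitivity analysis only.
- **MTPM.** Enter the pre-revision value at the time it was measured, not as a 2-year value. A Mann-Whitney test at 2 years then has no value for a patient whose glenoid component was removed. So prespecify a sensitivity analysis that gives patients revised for glenoid loosening the worst rank, and report it beside revision counts by arm.
- **Early drop-outs.** Delete the 3-month exclusion for WOOS. Make the promised missing-data analysis a delta or tipping-point analysis that includes these patients, since their baseline scores alone do not remove bias.

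The cost is wording and slightly more analysis work; the visits are already planned. The result may become less favourable to the arm with more failures.

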### Modification of the protocol

Any protocol modifications which might have an impact of the study will immediately be reported to all investigators and trial registries.

### Statistics

Prior to the analysis, the nature of the data is assessed. It is expected to analyse the changes between pre- and postoperative assessment with paired parametric statistics. The differences between the groups are expected to be analysed using parametric statistics (Student *t*-test). The radiostereometric analysis data is not expected to be normally distributed and will be analysed using non-parametric analysis of variance over time. The differences between these groups will be analysed with Mann-Whitney *U* test. Because of the nature of repeated measures in this study, it is expected to use a mixed effects model to analyse the overall results. Data on radiostereometric analysis and DXA will be analysed at the end of follow-up for the first 56 patients. No other interim data-analysis will be carried out.

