### Sequence generation and allocation

The randomization done on the trial laptop is done in the Research Electronic Data Capture (REdCap), in which the computer generates the randomization sequence by block randomization, stratified for gender and age and equally randomized to both shoulders (1:1 allocation). The primary investigator reads the allocation from the trial laptop to inform the surgeon. An independent statistician prepares the randomization table before the study is initiated.

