#### Primary functional outcome

*WOOS score*: The WOOS score is a disease-specific patient-reported outcome [18]. It contains 19 questions, divided into four groups: sports and work, physical symptoms, emotions, and lifestyle. The questions are answered using a visual analogue scale ranging from 0 to 100. The overall score is from 0 to 1900, where 1900 is the worst result. The scores are converted into a percentage of the maximum score to ease the interpretation. The difference in mean score between the preoperative score and the 2-year follow-up score is the primary value of interest. In this study, there is used a version of WOOS, which has been translated to Danish according to the guidelines of Guillemin, Bombardier and Beaton [19]. This version has been validated with classical test theory in a cohort of patients treated with shoulder arthroplasty for osteoarthritis [21].

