### Sample size calculation WOOS

The standard deviation of WOOS is set at 15 (15% of a maximum score). The minimally clinically important difference is set at 10 (10% of a maximum score), the significance level is set at 5% and the power of 0.90. With these assumptions, 48 patients are needed in each group resulting in a study population with 122 participants [26] (allowing for 20% drop-out). MCID of WOOS for patients with reverse shoulder arthroplasty for degeneration of the glenohumeral joint with either rotator cuff insufficiency or severe posterior glenoid wear has not been defined. Thus, the estimates used in the sample size calculation were based on studies which included patients with an anatomical total shoulder arthroplasty for osteoarthritis [27, 28].

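### The co-primary WOOS comparison has no settled primary analysis, and the SD of 15 behind its sample size is not identified as that of the score or of the change; adjusting for baseline removes the resulting doubt about power

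*Protocol article*

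**What the plan says.** All references are to the protocol article.

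- **Primary functional outcome** sets the target for WOOS: "The difference in mean score between the preoperative score and the 2-year follow-up score is the primary value of interest".
- **Statistics** says of between-group comparisons: "The differences between the groups are expected to be analysed using parametric statistics", and names the Student t-test. No baseline covariate is mentioned. Because measures are repeated, the same paragraph adds that "it is expected to use a mixed effects model to analyse the overall results".
- **Protocol violations, revision and drop-out** says of someone who leaves the trial: "The patient in question will be included in the final mixed-effect model analysis", except for those who leave before 3 months. Revised patients enter the 2-year analysis with their last available assessment.
- **Sample size calculation WOOS** describes the variability in these words: "The standard deviation of WOOS is set at 15 (15% of a maximum score"). The target is a 10-point difference on the percentage scale, tested at the 5% level with 0.90 power. The result is 48 per group, or 122 in all with 20% drop-out. The estimates come from studies of anatomical shoulder arthroplasty. No pre-post correlation is given.
- **Sequence generation and allocation** describes allocation "by block randomization, stratified for gender and age".

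**The concern.** Two things are left open in the text, and they interact.

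First, two analyses are named for the same co-primary outcome, with no statement of which one decides. They can give different answers. A t-test on the 2-year change needs a 2-year value for each patient, whereas the mixed model is said to retain patients who leave after 3 months. With 20% drop-out planned for, the choice could matter, and it should not be made after the data are seen.

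Second, the variability that drives the sample size depends on the analysis. The SD of a change from baseline equals the SD of the score only at one particular correlation between the two measurements. The sample size section speaks simply of the SD of WOOS. Read as the SD of the score, that does not match a comparison of changes unless the correlation happens to be right.

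Validity is not at stake: under randomization the t-test on change is unbiased and keeps its type I error. What is at stake is precision for a co-primary outcome, and a clear answer to which result counts.

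**Working it through.** **Inputs from the article:** difference 10, SD 15, 5% significance, power 0.90, 48 evaluable per group, 20% drop-out, 1:1 allocation. A two-sided test is assumed because it reproduces the stated size; one-sided would give 39 per group. **Assumed:** the pre-post correlation r, shown from 0 to 0.7.

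**Step 1: reproduce the stated figure.** n per group = 2 × (1.960 + 1.282)² × (15/10)² = 2 × 10.51 × 2.25 = 47.3, so 48. This matches. The t distribution gives 48.3. For drop-out, 48/0.8 = 60 per group, or 120; rounding up to 49 gives 62 per group, or 124. The stated 122 lies between, so the arithmetic is sound. It contains no correlation term.

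**Step 2: SDs under two analyses, taking 15 as the score SD at both times.**

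- Change score: SD = 15 × √(2(1 − r))
- Baseline-adjusted: SD = 15 × √(1 − r²)
- Power (normal approximation) = Φ(10 / (SD × √(2/48)) − 1.96)

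Example at r = 0.3: SD of change = 15 × √1.4 = 17.75; standard error = 17.75 × 0.2041 = 3.62; 10/3.62 − 1.96 = 0.80; power 0.79, or 0.78 with the t distribution.

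| r | SD of change | Power, change (t) | Power, change (normal) | n per group for 0.90 (normal) | Adjusted SD | Power, adjusted (normal) |
|---|---|---|---|---|---|---|
| 0 | 21.21 | 0.63 | 0.64 | 95 | 15.00 | 0.90 |
| 0.2 | 18.97 | 0.72 | 0.73 | 76 | 14.70 | 0.92 |
| 0.3 | 17.75 | 0.78 | 0.79 | 67 | 14.31 | 0.93 |
| 0.4 | 16.43 | 0.84 | 0.85 | 57 | 13.75 | 0.95 |
| 0.5 | 15.00 | 0.90 | 0.90 | 48 | 12.99 | 0.97 |
| 0.6 | 13.42 | 0.95 | 0.96 | 38 | 12.00 | 0.98 |
| 0.7 | 11.62 | 0.99 | 0.99 | 29 | 10.71 | 1.00 |

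The break-even for 0.90 power with 48 per group is r = 0.49 (normal) or 0.50 (t).

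**Step 3: how firm is the 0.5 threshold?**

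- With no drop-out (122/2 = 61 per group) the break-even falls to about 0.36, and t-based power at r = 0.3 is 0.87.
- If the 2-year SD is 15 but the preoperative SD is s, the SD of change equals 15 when s² + 225 − 30rs = 225, that is, r = s/30. Assumed values of s = 10 and s = 20 give 0.33 and 0.67.

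**Step 4: the other reading of 15.** If 15 is the SD of the change, Step 1 is already the power of the change-score test, with no condition on r. Baseline adjustment estimates the slope on baseline instead of fixing it at 1, so its residual SD cannot exceed the SD of change, apart from one degree of freedom. It is therefore at least about as precise under this reading too.

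**Step 5: the mixed model.** Its power depends on how baseline enters. With a freely estimated baseline mean in each arm, the 24-month contrast is essentially the change-score contrast and the condition on r roughly remains. With baseline as a covariate, or constrained equal across arms, it behaves like the adjusted column. The article does not say which is meant.

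**The case against.** A reader might infer that the WOOS primary analysis is an unadjusted t-test and that the trial is therefore underpowered. The documents do not support that.

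- The t-test is only expected, subject to a look at the data, and the drop-out section points towards the mixed model as final. A mixed model that handles baseline well has no shortfall.
- The article never says that 15 is the SD of the score. Since the change is the value of interest, 15 may have been meant as the SD of change, and the cited sources cannot be checked here.
- The 0.5 threshold needs equal SDs at both times and exactly 48 evaluable per group. No document figure shows that r lies below 0.5.

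All three points stand, so the power loss is conditional.

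It can also be said that covariates are commonly left to an analysis plan, which is not shown. That is fair: their absence alone is no finding. It does not answer the rest, because the article itself names two analyses for one co-primary outcome and gives an SD that can be read two ways. Likewise, the article does not state that the t-test would use complete cases only; that is inferred from its needing a 2-year value. A sensitivity analysis for missing data is planned.

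On stratification, an analysis that ignores gender and age gives standard errors that are too large only to the extent that these factors predict WOOS. The article gives nothing from which to size that.

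**Conclusion.** The ambiguity is real; a power failure is not shown. Two analyses are named for WOOS without saying which is primary, and the SD of 15 is not identified.

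If 15 is the score SD, equal before and after surgery, with 48 evaluable per group, a change-score analysis falls short of 0.90 power when r is below about 0.5: about 0.84 at r = 0.4, 0.78 at r = 0.3 and 0.63 at r = 0. If 15 is the SD of the change, the stated power stands. The calculation of 48 per group is not an error under either reading.

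Baseline adjustment keeps power at about 0.90 or above across the whole range, provided that the 2-year SD is 15 (or, under the other reading, the SD of change is 15). This is a clarification together with a free gain in precision. It is worth making for a co-primary outcome, but it is not a fault that invalidates the design.

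**What to change.** 1. Name one primary WOOS analysis: a mixed model on the post-operative WOOS values with arm, visit and arm-by-visit, adjusted for baseline WOOS and for gender and age as used in the stratification. Report the 24-month difference between arms with its 95% confidence interval.
2. Make the t-test on change a sensitivity analysis.
3. In the WOOS sample size section, state whether 15 is the SD of the score or of the change, after checking the source studies. The answer should not be presumed. If it is the score SD, add that the planned analysis adjusts for baseline, so that 48 per group remains sufficient.

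**Cost:** wording only, to be settled before the data are unblinded. Baseline WOOS, age and gender are already collected, and no patients or visits are added.

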## Methods and design

### Study design

This study is an investigator initiated, single-centre, 1:1 randomized controlled trial, which will compare the DELTA Xtend® Reverse Shoulder Lateralized Glenosphere Line Extension (intervention group) with the standard DELTA Xtend® Reverse Shoulder System (control group). The two implants are produced by Depuy Synthes (Raynham, MA, USA). The SPIRIT reporting guidelines [20] and checklist (Additional file 1: Appendix 1) were used.

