### Method

Inclusion criteria:Rotator cuff arthropathy defined as degeneration of the glenohumeral joint and wear or tear of at least one rotator cuff tendonDegeneration of the glenohumeral joint with intact rotator cuff function but severe posterior wear of the glenoid (> 20° posterior wear)Insufficient effect of non-surgical treatment with symptoms severe enough to justify shoulder arthroplasty.ASA (American Society of Anesthesiology) score 1–3, physically fit for surgery and rehabilitation

Exclusion criteria:Below 50 years of ageCognitive or linguistic impairmentInsufficient glenoid bone-stockPrevious fracture in the upper extremitiesPatients with autoimmune-mediated inflammatory arthritisGlenoid border medial to the medial border of the coracoid on a true AP radiograph (Fig. 1)

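### Two diagnoses are pooled, but diagnosis enters neither the stratification nor the named between-group tests; if it predicts WOOS change or migration, precision is lost that a prespecified covariate would recover

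*Protocol article*

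**What the plan says.** - **Eligibility (Method, repeated under Enrolment).** One route in is rotator cuff arthropathy, defined by wear or tear of at least one cuff tendon. The other is joint degeneration with "intact rotator cuff function but severe posterior wear of the glenoid", set at more than 20°.
- **Randomisation (Sequence generation and allocation).** It is "block randomization, stratified for gender and age". Diagnosis is not a factor.
- **Between-group tests (Statistics).** "The differences between the groups are expected to be analysed using parametric statistics", with the Student t-test named. For the radiostereometric data: "The differences between these groups will be analysed with Mann-Whitney" U.
- **Mixed model (Statistics).** Because measures are repeated, "it is expected to use a mixed effects model to analyse the overall results". No covariate is listed. The section on protocol violations, revision and drop-out treats a mixed model as the final analysis.
- **Subgroups (Surgical procedure).** The only one named compares the first and second half of the patients, for the learning curve.
- **Planning values.** WOOS: SD 15, difference 10, 48 per group. MTPM: SD 0.4 mm, difference 0.4 mm, 22 per group. Both use 5% significance and power 0.90. The WOOS sample size section says that the minimally clinically important difference for reverse arthroplasty patients "with either rotator cuff insufficiency or severe posterior glenoid wear has not been defined", and that the estimates come from studies of anatomical arthroplasty for osteoarthritis.

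**The concern.** The two diagnoses differ in cuff status and in glenoid bone. Cuff status plausibly bears on how much function improves, and glenoid bone on how the glenoid component migrates. These are the two co-primary outcomes. If either link is real, the variation between diagnoses sits in the error term of a two-sample test that has no place for it, and an uneven split of diagnoses between arms moves the estimated treatment difference. Diagnosis is an eligibility criterion, so it is known for every patient before randomisation, and using it needs nothing extra. The stratification factors are fixed in the text, and the two named tests are unadjusted by construction. The point is therefore about what is stated, not only about a covariate list that may be written elsewhere.

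**Working it through.** **1. The plan's own figures.** With n = 2(z₀.₉₇₅ + z₀.₉₀)²(SD/Δ)² and z-sum 3.2415:
- WOOS: 2 × 10.507 × (15/10)² = 47.3, so 48 per group.
- MTPM: 2 × 10.507 × (0.4/0.4)² = 21.01, so 22 per group.

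Both match. With 20% drop-out, 28 per group gives 56. For WOOS, 96/0.8 = 120; the exact t-test needs 48.3, hence 49 per group, and 98/0.8 = 122.5, close to the stated 122. There is no arithmetic error.

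**2. Effect of ignoring diagnosis, if the planning SD is a within-diagnosis value.** Let p be the share with posterior wear and D the difference between diagnoses in mean 2-year WOOS *change*. Change is what matters, because the section on the primary functional outcome makes it the value of interest. Both p and D are assumptions; the article gives neither.

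SD_total = √(SD² + p(1−p)D²). Power is from the two-sided t-test with 48 per group and Δ = 10.

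| p | D (points) | p(1−p)D² | SD_total | Power |
|---|---|---|---|---|
| any | 0 | 0 | 15.0 | 0.898 |
| 0.05 | 5 | 1.19 | 15.04 | 0.897 |
| 0.15 | 5 | 3.19 | 15.1 | 0.894 |
| 0.15 | 10 | 12.75 | 15.4 | 0.882 |
| 0.25 | 15 | 42.19 | 16.3 | 0.843 |

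Adjusting for diagnosis returns the residual SD to 15 and power to about 0.90.

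**3. If SD 15 already covers the mixture.** Planned power is intact and adjustment only adds to it. At p = 0.15 and D = 10, the residual SD is √(225 − 12.75) = 14.6, and power goes from 0.898 to 0.914.

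**4. Migration.** The same formula with SD 0.4 mm, Δ = 0.4 mm and 22 per group gives power 0.900 at D = 0. It gives 0.891 at p = 0.15, D = 0.2 mm (SD_total 0.406), and 0.844 at p = 0.25, D = 0.4 mm (SD_total 0.436). These are t-test figures for a comparison of means. The planned test is Mann-Whitney U, so they show only the order of size.

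**5. Chance imbalance.** The standard error of the between-arm difference in diagnosis share is √(2p(1−p)/n). Two standard errors are:
- WOOS, 48 per group: 15 percentage points at p = 0.15 and 18 at p = 0.25.
- Migration, 22 per group: 22 and 26 percentage points.

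The radiostereometric part is thus √(48/22) ≈ 1.5 times as exposed. Multiplied by D, a two-standard-error imbalance moves the WOOS difference by 0.146 × 10 = 1.5 points or 0.177 × 15 = 2.7 points, against the 10-point target.

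**6. Steps 2 and 5 are one effect.** At p = 0.25 and D = 15, the squared standard error rises from 2 × 225/48 = 9.375 to 2 × 267.19/48 = 11.133, a rise of 1.758. The imbalance term is 2p(1−p)D²/48 = 2 × 0.1875 × 225/48 = 1.758. The imbalance shift restates the lost precision and must not be added to it.

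**The case against.** **The mixed model could carry diagnosis.** Its covariates are unlisted, not excluded, and an analysis plan that is not shown may name them. The Statistics section is also worded largely as expectation. This stands as far as it goes: a reader might infer that diagnosis will certainly go unadjusted, and the text does not show that. It does not rescue the two named tests, which cannot take a covariate, or the stratification factors, which are fixed.

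**The loss may be nil.** A stable difference in WOOS level between diagnoses cancels in a change score; only a different improvement matters. The article supports no value for that, nor for any difference in migration. The share could be small as well: the centre expects 75 rotator cuff arthropathy operations a year, or 150 over the two-year recruitment window, which already exceeds 122. Bone-stock and medialisation exclusions apply to all patients and narrow any difference in glenoid support. All of this stands and makes the point conditional.

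**The SD may already cover the mixture.** The article says only that the estimates were based on anatomical-arthroplasty studies. Whether 15 is a within-diagnosis value cannot be checked from the text. This stands too.

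**The tests are valid.** Randomisation protects type I error. This is a matter of efficiency and conditional balance.

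**The categories may overlap.** One is defined by tendon wear or tear, the other by intact cuff function. A shoulder with a worn tendon, preserved function and more than 20° of posterior wear could meet both. This stands and belongs in the fix.

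**Conclusion.** The point holds in conditional form. Two diagnoses are pooled, diagnosis is not a stratification factor, the named t-test and Mann-Whitney U cannot use it, and no covariate is named for the mixed model. If diagnosis predicts the 2-year WOOS change or MTPM, precision is given up and the result is more open to an uneven split, chiefly in the radiostereometric part.

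A reader might infer that both co-primary comparisons are underpowered. The article does not support that. The loss is zero at D = 0 and under half a power point at D = 5 with a share of up to 15%. It reaches 5 to 6 points (0.898 to 0.843) only with a 25% share, a 15-point difference in improvement and SD 15 read as within-diagnosis. Lower figures need a still larger share and difference, for which there is no source. The case for acting is that the change costs almost nothing and is credible only if made before the data are seen.

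**What to change.** In the Statistics section:
1. Prespecify diagnosis as a fixed covariate in the mixed model (or an ANCOVA) used for the between-group WOOS comparison.
2. For migration, replace the plain Mann-Whitney U comparison with a covariate-adjusted rank-based analysis (Quade type) or a model for log-MTPM that includes diagnosis.
3. State which category applies when a shoulder meets both definitions, with the classification fixed before randomisation.
4. Report the number of each diagnosis by arm, for all patients and for the radiostereometric subset.

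The cost is a few sentences and one degree of freedom per analysis. It needs no new data and no change to the randomisation or the sample size.
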